	All patients in our defined cohort; all patients grouped by CPCSSN case definition	Overall number and types of referrals; proportion referred to cardiology, endocrinology (as appropriate for condition)				
**Investigations performed**				Appropriateness		Laboratory
	All patients in our defined cohort	Number of vitamin D, CBC^e^, eGFR^f^, ACR^g^, and liver function tests performed				
	Patients with CKD^h^	Number with and frequency of eGFR and ACR tests				
	Patients without diabetes	Number with HbA_1c_^i^, FBS^j^ measured (screening)				
	Patients taking or not taking statins	Number with and frequency of lipid panel/LDL^k^				
	Patients taking or not taking levothyroxine	Number with and frequency of TSH^l^ measured				
	Patients with the CPCSSN case definition of diabetes	Proportion with HbA_1c_ measured every 6 months and every 12 months				
**Monitoring results**				Appropriateness		Examination
	All patients in our defined cohort; all patients grouped by CPCSSN case definition and age	Proportion with BP ≤140/90 or ≤130/80 (as appropriate based on chronic conditions and age); proportion of patients in the following sBP^m^ ranges: ≤130, 131-140, 141-150, 151-160, and >160				
**Medications**				Comprehensiveness and appropriateness		Medication and risk factor
	Patients with the CPCSSN case definition of diabetes	Proportion of patients with and overall number and frequency of metformin prescriptions, insulin prescriptions, and other oral antidiabetic prescriptions^n^				
	Patients with the CPCSSN case definition of HF	Proportion of patients with and overall number and frequency of β-blocker prescriptions, ARB^o^ prescriptions, and ACE-I^p^ prescriptions				
	Patients who smoke	Number of patients with NRT^q^ prescription				

^a^CPCSSN data table.

^b^CPCSSN: Canadian Primary Care Sentinel Surveillance Network.

^c^HF: heart failure.

^d^BP: blood pressure.

^e^CBC: complete blood count.

^f^eGFR: estimated glomerular filtration rate.

^g^ACR: albumin-to-creatinine ratio.

^h^CKD: chronic kidney disease.

^i^HbA_1c_: hemoglobin A_1c_.

^j^FBS: fasting blood sugar.

^k^LDL: low-density lipoprotein.

^l^TSH: thyroid-stimulating hormone.

^m^sBP: systolic blood pressure.

^n^Other oral antidiabetic medications include classes such as sodium-glucose cotransporter-2 inhibitors, sulfonylureas, meglitinides, dipeptidyl peptidase 4 inhibitors, etc.

^o^ARB: angiotensin receptor blocker.

^p^ACE-I: angiotensin-converting enzyme inhibitor.

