^q^NRT: nicotine replacement therapy.

*Access* to the practice will be measured as the overall number of encounters.

*Comprehensiveness* refers to primary care addressing “all problems in the population (with short-term referral as needed), except those that are too unusual (generally a frequency of less than 1 or 2 per thousand in the population served) for the primary care practitioner or team to treat competently” [1]. As indicators of comprehensiveness, we will measure number of different diagnoses addressed per patient per year, proportion of patients’ chronic conditions addressed at least once a year, number of pneumococcal vaccines and influenza vaccines in patients 65 years or older, and number of prescriptions for nicotine replacement therapy

*Appropriateness* will be examined in 2 ways: laboratory tests that are indicated for monitoring of chronic conditions but may be ordered more frequently than necessary (eg, hemoglobin A_1c_ in diabetics) and laboratory tests that are frequently ordered routinely (or for screening purposes) but may be overused in certain populations, including thyroid function tests, vitamin D, albumin-to-creatinine ratio, and lipid panel testing [53]. We hypothesize that some of these tests, while indicated at a base frequency, may be commonly overused; thus, their frequency may have declined during the pandemic.

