Diabetes and heart failure are 2 chronic conditions where aspects of care can be reasonably evaluated in CPCSSN. We will describe care across the population in terms of frequency of contacts, laboratory tests and investigations, and medications prescribed that would suggest care that is in step with evidence-based recommendations [54]. For patients with diabetes, we will measure the percentage of patients with a diabetes-related encounter every 6 and 12 months; percent with a foot examination in the last 12 months; percent with a blood pressure measure and hemoglobin A_1c_ test every 6 and 12 months (and results); percent with influenza vaccination; overall number of diabetes-related investigations; percent referred to endocrinology; percent receiving, and number and frequency of metformin, insulin, and other antidiabetic prescriptions. For patients with heart failure, we will measure percentage of patients with heart failure–related encounters every 6 and 12 months; number of investigations (echocardiogram and blood tests); percent with a blood pressure measure every 6 and 12 months (and results); percent with influenza vaccination; percent receiving β-blocker, angiotensin-converting enzyme inhibitors, and angiotensin receptor blockers; and percent referred to cardiology and other specialists.

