## Discussion

### Key Findings

The aim of this study is to help identify signals of change across several domains of primary care, including access, comprehensiveness, and appropriateness, that may have occurred in response to the COVID-19 pandemic. This will be done by investigating the overall number of primary care encounters during the pandemic compared with prepandemic, as well as potential changes in the number of diagnoses addressed during encounters, number of blood pressure measurements, number of vaccines provided, number of blood tests carried out, and so on. Potential changes in indicators specific to the management of chronic conditions will also be investigated, for example, frequency of HbA_1c_ testing for those with diabetes, number and frequency of visits for monitoring of heart failure, and number of prescriptions for diabetes or heart failure. Potential changes in any of these indicators may indicate that gaps in care are present that may benefit from targeted recovery measures.

However, these potential changes in primary care are not inherently negative. For example, many blood tests, examinations, and procedures are considered overused in certain populations and may be conducted more frequently than necessary [53,57,58]. If decreases in number or frequency of these overused tests are identified during the pandemic, this may be considered more appropriate use when compared to prepandemic levels. Furthermore, decreases in frequency of certain primary care interventions may not be clinically significant or necessarily lead to negative health outcomes. Therefore, it is important that each identified change be carefully considered in a broad clinical context before firm conclusions can be drawn.

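### HbA1c in diabetes is the protocol's example of a test ordered too often, but its specific indicator records only whether a test was done, not how many

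*Protocol article*

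**What the plan says.** All references are to the protocol article.

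- **The question.** The appropriateness paragraph under Outcome Definitions and Measures sets out two ways of examining appropriateness. The first concerns tests that have a place in monitoring chronic disease but that "may be ordered more frequently than necessary", and HbA1c in patients with diabetes is the only example given. The paragraph then states: "We hypothesize that some of these tests, while indicated at a base frequency, may be commonly overused; thus, their frequency may have declined".
- **The indicator.** In Table 1, under investigations performed (source: Laboratory), the row for patients with diabetes reads "Proportion with HbA_1c_ measured every 6 months and every 12 months". The paragraph on diabetes and heart failure in the same section repeats it as a percentage and adds the test results.
- **The neighbouring rows.** In the same block of Table 1, lipids have "Number with and frequency of lipid panel/LDL". TSH, and eGFR and albumin-to-creatinine ratio in chronic kidney disease, are worded the same way. Vitamin D, blood count, eGFR, albumin-to-creatinine ratio and liver function tests have counts for the whole cohort.
- **The Discussion.** Key Findings lists "frequency of HbA_1c_ testing for those with diabetes" among the indicators to be investigated.

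**The concern.** The hypothesis is about how often a test is done once a base frequency has been met. The indicator is yes/no: it reaches its maximum at the first test in each interval and gives no weight to any later one. Those later tests are what an overuse question is about. The test chosen as the example is thus the one whose specific indicator cannot address it, and the frequency named in the Discussion has no matching definition in the Methods.

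What is at stake is interpretation. Key Findings allows that a drop in an overused test may mean more appropriate use, and also that a change in any indicator may signal a gap in care. For HbA1c in diabetes, the coverage proportions alone give no means of telling the two apart.

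**Working it through.** The plan gives no HbA1c test rate, so there is no figure of its own to reproduce on this point. The sample sizes under Statistical Analysis and Power do not depend on it. The check sets the passages against each other and then illustrates how the indicator behaves.

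**1. Match between question and measure**

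| Test named in the appropriateness paragraph | Measure in Table 1 | Sees tests beyond the first? |
|---|---|---|
| Vitamin D | count | yes |
| Albumin-to-creatinine ratio | count; number and frequency in kidney disease | yes |
| Lipid panel | number and frequency | yes |
| Thyroid function | number and frequency of TSH | yes |
| HbA1c in diabetes | proportion tested per 6 and 12 months | no |

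**2. Behaviour of the indicator (test rates are assumptions)**

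*Evenly spaced tests, 4 falling to 2 a year.* Every patient still has at least one test in each 6-month window. Both proportions stay at 100% while volume falls by (4 − 2)/4 = 50%.

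*Poisson timing, mean m a year, 4 falling to 3.*

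- One 6-month window, 1 − exp(−m/2): 1 − exp(−2) = 86.5%; 1 − exp(−1.5) = 77.7%. Change −8.8 points.
- Both 6-month windows of a year, if that is what the indicator means, [1 − exp(−m/2)]²: 74.8% to 60.4%.
- 12 months, 1 − exp(−m): 98.2% to 95.0%.

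**3. What the 8.8 points can and cannot show**

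Per 6-month window, the mean number of tests is m/2 and the mean number of first tests equals the coverage, so tests beyond the first = m/2 − coverage.

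- Before: 2 − 0.865 = 1.135. After: 1.5 − 0.777 = 0.723. Fall: 0.412.
- Total fall: 2 − 1.5 = 0.5 tests per window, or 25%. First tests account for 0.088 of this, and tests beyond the first for 0.412, which is 0.412/0.5 = 82%.

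Now take a different change from the same starting point. Patients making up 8.8% of the cohort, who had exactly one test in the window, lose it, and nobody else changes. This is possible because the Poisson share with exactly one test is 2·exp(−2) = 27.1%. Coverage again falls from 86.5% to 77.7%, but volume falls by only 0.088/2 = 4.4% and no test beyond the first is lost.

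The indicator returns the same result for a 25% fall made up mostly of repeat tests and for a 4.4% fall made up wholly of lost coverage. A count per patient separates them.

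**The case against.** The strongest reply is that the protocol does provide for counting.

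- Table 1 twice lists, for patients with diabetes or heart failure, the number and types of condition-related investigations, once under a domain that includes appropriateness. The text repeats the number for diabetes. For heart failure, it says that investigations include blood tests, so HbA1c would be a natural member of the diabetes set. This stands in part. Those rows do not name HbA1c, and their stated source is the encounter, encounter diagnosis and billing tables, not Laboratory. The overall number in the text would also pool HbA1c with other tests.
- The diabetes and heart failure paragraph says that care will be described by how often contacts and tests occur, and Key Findings names HbA1c frequency. This shows the intent, but no indicator is defined to carry it out. The 30-day interval rates under Primary Exposure are for selected outcomes, and HbA1c is not named.
- A condensed article may leave definitions to a fuller plan. That is fair for what counts as a diabetes-related investigation. It does not explain why this row of the outcome table is worded differently from its neighbours.

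A reader might also infer three stronger points, which the document does not support:

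- *That the overuse hypothesis cannot be tested.* It concerns some of these tests, and the other four named have counts or frequencies.
- *That a fall would be reported as lost care.* Key Findings says that a drop in an overused test may be more appropriate use and that each change needs clinical context. Moreover, part of the Poisson fall is a true loss of coverage, which the indicator reports correctly.
- *That an 8.8-point fall matters because it exceeds the 5-point change in the power section.* The change from 50% to 55% there is a sample-size example, not a threshold for a care gap.

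**Conclusion.** The point holds for HbA1c in diabetes only. Its specific indicator measures minimum coverage, while the appropriateness paragraph uses this test to illustrate excess and the Discussion promises its frequency. With the coverage proportions alone, a fall in repeat testing is either unseen (volume halved, both proportions at 100%) or mixed with lost coverage (the same 8.8-point fall fits a 25% or a 4.4% fall in volume). The pooled investigations count covers the gap only in part.

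These sizes rest on assumed rates of 4, 3 and 2 tests a year and on evenly spaced or Poisson timing. They show how the measure behaves and do not forecast the result. A test beyond the first in a window is also not necessarily an unnecessary one. No sample-size figure changes. The point is modest, but worth acting on because the plan cannot otherwise answer its own question for the test it chose as the example.

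**What to change.** - Keep the 6- and 12-month proportions and label them as the under-testing indicator.
- Add to the HbA1c row for diabetes in Table 1 the number and frequency of HbA1c tests from the Laboratory table: tests per person-year, and the distribution of tests per patient per year, each before and during the pandemic. Person-time also accommodates patients who die during follow-up.
- State that these measures, not the coverage proportions, address the overuse hypothesis for HbA1c.
- Make Table 1, the diabetes paragraph of the Methods and Key Findings say the same thing, and state whether the diabetes-related investigations count includes HbA1c.

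No minimum repeat interval is proposed here. If the investigators want a threshold for excess testing, it is for them to prespecify it from the recommendations they cite.

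The cost is one or two more reported indicators and a few lines of code. The Laboratory table is already the source for this row, and at the time of writing (May 2023) only exploratory analyses had begun.

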### Statistical Analysis and Power

As of 2018, there were 1.13 million adult patients in the CPCSSN database, with 65% (734,500/1,130,000) having at least 1 chronic condition [55]. A sample size of 1276 paired (pre-post) individuals would be required to detect a change from 50% to 55% of patients experiencing an outcome, with a correlation between paired observations of 0.2 [56]. With a correlation between pairs of 0.1, the required sample size would be 1432. We expect to have adequate sample size to examine changes within specific conditions given the approximate prevalence of hypertension (22%), diabetes (10%), chronic obstructive pulmonary disease (4%), and heart failure (4%) among adults in CPCSSN data or other Canadian data [13,55].

#### Descriptive Analyses

To describe the cohort, continuous or count variables will be analyzed for their mean, median, SDs, and IQRs. For categorical variables, percentages will be calculated. We will present outcomes stratified by sex, age category (40-49, 50-59, 60-69, and ≥70 years), urban versus rural patient address, and neighborhood income quintile (1-2 [lower] vs 3-5 [higher]).

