**Methods:**

This is a retrospective, single-arm, pre-post study using Canadian Primary Care Sentinel Surveillance Network (CPCSSN) data. CPCSSN is a research network supported by a primary care electronic medical record database, comprising over 1500 physicians and nearly 2 million patients. We are examining changes in care (eg, frequency of contacts, laboratory tests and investigations, referrals, medications prescribed, etc) among adults. We will also examine indicators specific to evidence-based recommendations for care in patients with diabetes and those with heart failure. We will compare rates of outcomes during key periods of the pandemic between March 13, 2020, and December 31, 2022, with equal time periods before the pandemic. Differences will be examined among specific subgroups of adults, including by decade of age, number of comorbidities, and socioeconomic status. Regression models appropriate to outcome distributions will be used to estimate changes, adjusting for potential confounders. This analysis is part of a mixed-methods study with a qualitative component investigating how patients with diabetes with or without concurrent heart failure perceived the impact of the pandemic on access to primary care and health care–related decisions. This study was approved by the Hamilton Integrated Research Ethics Board (14782-C).

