### Study Population

The study population is all patients who were 18 years and older in 2018, and some analyses will focus on subgroups of patients with specific chronic conditions. We will use the 2-year contact population as recommended previously for defining practice populations for primary care [49]. This method uses contacts within encounter, medication, and billing-related data tables, and has been used previously with CPCSSN data to produce national chronic disease estimates [50]. This method will be used in the period from March 13, 2018, to March 13 2020. We will use this population rather than the full CPCSSN patient population data (dating back more than 2 decades for some networks) to limit the size of the data set, while maintaining the patient population that is likely to have a relationship with a primary care practice during the study period. Although this approach may exclude patients who are younger, healthier, and less likely to seek primary care compared with patients with chronic conditions, we do not expect this to have a major impact on findings because this study focuses on the age group where chronic condition prevalence begins to increase and where screening guidelines apply (eg, diabetes). Therefore, this age group is more likely to see a primary care physician regularly.

People who died during the study period will be included up to the point of death using the death date if captured or the presence of a deceased status with date estimated from the most recent contact in CPCSSN data. Patients who were older than 105 years at the start of the COVID-19 pandemic will be excluded as a possible data error.

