#### Analyses of Changes Over Time

We will present the proportions of patients experiencing the outcomes for each time period or mean changes for continuous variables and 95% CIs. Statistical significance of changes from pre to post time period will be assessed using the McNemar test for binary variables, the Wilcoxon signed rank test for original variables, and the paired *t* test for continuous variables. Regression models appropriate to outcome distributions will be used to control for potential confounders of age (<70 vs ≥70 years), sex, count of comorbidities (CPCSSN-validated conditions), neighborhood income quintile, and CPCSSN network (corresponding to location within Canada). Interactions will be examined in the descriptive analysis and will be considered for inclusion in models if they are found to be relevant. We will present adjusted estimates and 95% CIs for outcomes and parameter estimates for the independent variable and covariates. Analyses will be completed using SAS (version 9.4; SAS Institute, Inc).

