## Results

### Study Timeline

The start date of this study was October 5, 2022, and the prospective end date is January 31, 2024. At the time of writing (May 2023), we have finished data cleaning and begun exploratory analyses. As there are known consistencies with CPCSSN data, having a longer exploratory analysis phase has allowed us to liaise with central CPCSSN data managers in order to prepare data for the main analyses. We have now also defined our study cohort: a total of 875,934 individuals between the ages of 18 and 105 years as of 2018 were included.

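### The age strata start at 40 in a cohort aged 18 to 105, and the models carry age only as a cut at 70, so change by age among younger adults cannot be reported

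*Protocol article*

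**What the plan says.** The protocol article describes age in five places.

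- Study Population, eligibility: "The study population is all patients who were 18 years and older in 2018".
- Results, Study Timeline, the cohort as already defined: "a total of 875,934 individuals between the ages of 18 and 105 years as of 2018 were included".
- Abstract, Methods, the subgroup promise: "Differences will be examined among specific subgroups of adults, including by decade of age, number of comorbidities, and socioeconomic status".
- Descriptive Analyses, the strata for presenting outcomes: "age category (40-49, 50-59, 60-69, and ≥70 years".
- Analyses of Changes Over Time, the regression term: the models will "control for potential confounders of age (<70 vs ≥70 years", alongside sex, comorbidity count, income quintile and network.

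Study Population also argues that the contact rule's possible loss of younger, healthier patients matters little, because "this study focuses on the age group where chronic condition prevalence begins to increase".

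**The concern.** The strata do not cover the cohort. A table built to the Descriptive Analyses section has no row for anyone aged 18-39, and its age rows will not add up to the cohort total.

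The regression term is coarse for a different reason: it gives an 18-year-old and a 69-year-old the same age. The objectives ask whether changes were associated with sociodemographic characteristics and multimorbidity, and the analysis section says that estimates for the covariates will be reported. The Introduction itself notes that multiple chronic disease becomes more common with age. Age differences inside the under-70 group can therefore load onto the comorbidity count, and onto income or network where these are related to age.

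At stake are the age-specific answers for younger adults and the interpretation of the other covariate estimates. The overall pre-post change is not at stake.

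**Working it through.** The article gives no age distribution, so it has no figure of its own to reproduce on this point. The check has four steps.

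1. **Coverage.** Eligible ages start at 18 and the strata start at 40. The uncovered single years of age are 39 − 18 + 1 = 22. No section limits the age-stratified presentation to 40 and over. Against the abstract's promise of decades, the strata deliver 40-49, 50-59 and 60-69, then one open band from 70. The decades below 40 are missing.

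2. **Number of patients.** The share aged 18-39 is an assumption, taken as 20% to 40%:
   - 0.20 × 875,934 = 175,187
   - 0.30 × 875,934 = 262,780
   - 0.40 × 875,934 = 350,374

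   Two simple age distributions fall inside this range. Uniform from 18 to 90 gives 22/72 = 30.6%. Normal with mean 50 and SD 18, truncated to 18-105, gives 26.1% by simulation.

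3. **How coarse the cut at 70 is.** For the uniform case:
   - Share under 70 = 52/72 = 0.722.
   - Mean ages are 44 (under 70) and 80 (70 and over), a difference of 36 years.
   - Between-group variance = 0.722 × 0.278 × 36² ≈ 260.
   - Total variance = 72²/12 = 432.
   - Share of age variance captured = 260/432 ≈ 0.60.
   - SD of age left within the under-70 group = 52/√12 ≈ 15 years.

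   For the truncated normal case, simulation puts about 86% of patients under 70 and about 44% of age variance captured. These figures illustrate coarseness under assumed distributions. They do not measure bias in any planned estimate.

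4. **Interactions.** The analysis section says interactions will be looked for in the descriptive analysis and taken into models if relevant. With no descriptive stratum below 40, an age pattern there would not be seen. If period-by-age entered a model on the stated scale, it could separate only under 70 from 70 and over.

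**The case against.** The strongest reply is that the design protects the main result. This is a closed cohort compared with itself, using McNemar, signed rank and paired t tests, so a coarse baseline age term confounds the within-person change little. This stands. A reader might infer from the cut at 70 that the pre-post estimates are biased by age, and the documents do not support that.

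A reader might also infer that adults under 40 drop out of the study or out of its equity analysis. They do not. They stay in the all-patient outcomes, in the sex, rural or urban and income strata, and in the regressions as members of the under-70 group. They are missing only from the age-stratified presentation. The groups that the Conclusions name as expected to be disproportionately affected are older people and those of lower socioeconomic status.

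It may be tempting to read the strata and the Study Population rationale as remnants of a 40-and-over design. No text shows such a design. An intended but unstated focus on 40 and over for these tables would fit the wording equally well.

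Finally, subgroups by decade and a covariate cut at 70 serve different purposes, so those two statements do not contradict each other. The covariate form is a matter of analysis quality rather than a plain error. It also remains unshown that change, as opposed to level, varies with age below 70. However, whether it does is one of the things the study sets out to learn, and the stated term cannot reveal it.

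**Conclusion.** The coverage gap is certain from the text: patients aged 18-39 have no place in the age-stratified results, contrary to the abstract's promise for adults by decade. Its size, about 175,000 to 350,000 patients, rests on the assumed 20% to 40% share.

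The single cut at 70 is a weaker but sound second point. It leaves residual age confounding in the reported comorbidity, income and network estimates, of a size the documents do not allow anyone to compute, and it hides any age gradient in change below 70.

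The Study Population rationale needs the same alignment, since it describes a narrower age group than an 18+ cohort. The point deserves correction before the main analyses, but it does not threaten the primary pre-post comparison.

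**What to change.** - **Descriptive Analyses:** add 18-29 and 30-39 strata, or state that the age-stratified tables are limited to 40 and over and give the reason. If the limit is chosen, qualify the abstract's wording to match.
- **Analyses of Changes Over Time:** replace the two-level term with decade bands or a spline for age, and use the same scale for any period-by-age interaction.
- **Study Population:** rewrite the argument about younger, healthier patients so that it holds for adults from 18, or acknowledge the possible under-representation of that group as a limitation.
- **Record:** date the change and disclose it as made after data access, because the cohort was defined and exploratory analyses had begun by May 2023.

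Age is already in the data set. The cost is some revised wording, a few more parameters and table columns, and a documented amendment. Precision is not a constraint: even the low assumption of 175,187 patients under 40 is about 122 times the larger of the plan's two required sample sizes (175,187/1,432). If condition-specific cells turn out small, for example in heart failure, the two new bands can be merged into 18-39 for those tables.

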### Conclusions

We anticipate that this study will provide evidence that will inform whether and in what aspects of primary care the COVID-19 pandemic is associated with interruptions that may require attention. It will also highlight gaps or provide reassurance with respect to chronic condition care for populations who were expected to be disproportionately affected by pandemic health care changes such as those who are older or of lower socioeconomic status.

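### Outcomes are displayed by income only as quintiles 1-2 versus 3-5, which can hide differences in care change within each pooled group, although socioeconomic differences are a stated aim

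*Protocol article*

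**What the plan says.** Under Descriptive Analyses, the protocol article lists the variables by which outcomes will be stratified. Income appears there as "neighborhood income quintile (1-2 [lower] vs 3-5 [higher"]). This is the only place where the article sets out a display of outcomes by income.

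Under Analyses of Changes Over Time, income returns as a potential confounder in the regression models: "neighborhood income quintile, and CPCSSN network (corresponding to location within Canada"). No grouping is attached to it, whereas age is explicitly dichotomised in the same sentence. The section adds: "We will present adjusted estimates and 95% CIs for outcomes and parameter estimates for the independent variable and covariates". On effect modification it says: "Interactions will be examined in the descriptive analysis and will be considered for inclusion in models if they are found to be relevant".

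The aim is stated in the Methods part of the abstract: "Differences will be examined among specific subgroups of adults, including by decade of age, number of comorbidities, and socioeconomic status". The Conclusions section of the Discussion intends to identify gaps or give reassurance for "populations who were expected to be disproportionately affected by pandemic health care changes such as those who are older or of lower socioeconomic status".

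**The concern.** The study asks whether the change in care from before to during the pandemic differed by socioeconomic status. Under Strengths and Limitations the article accepts that individual socioeconomic data are rarely recorded, so equity analyses must lean on area-level indicators. Neighbourhood income is therefore the main equity variable, and the planned display reduces it from five levels to two.

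The regression covariate does not restore what is lost. A main effect of income describes how the level of care differs between income groups. Whether the pre-post change differs by income requires a period-by-income term, and the plan includes interactions only conditionally.

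At stake is how the results would be read. If the poorest fifth lost more care than the second fifth, the published tables would show only the average of the two. A modest two-group difference could then be read as reassurance about poorer patients.

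**Working it through.** **1. The plan's own sample-size figures.** Statistical Analysis and Power gives 1276 pairs for a change from 50% to 55% at correlation 0.2, and 1432 at correlation 0.1. The article states neither alpha nor power; I assume two-sided 0.05 and 80%.

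- Both events: p11 = p1·p2 + ρ·√(p1q1p2q2). At ρ = 0.2 this is 0.275 + 0.2 × 0.2487 = 0.3247.
- Discordant share: ψ = p1 + p2 − 2·p11 = 1.05 − 0.6495 = 0.4005. At ρ = 0.1, ψ = 0.4503.
- McNemar: n = (1.960·√ψ + 0.842·√(ψ − d²))² / d², with d = 0.05. This gives 1255.0 and 1411.2.
- Adding a continuity correction of 1/d = 20 and rounding up gives 1276 and 1432, the stated figures.

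The variance of an individual's pre-post change under these inputs (ρ = 0.2) is ψ − d² = 0.4005 − 0.0025 = 0.398. It is used in steps 3 and 4.

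**2. What the two-group contrast shows.** Let m1 to m5 be the mean change in each quintile. With equal-sized quintiles the contrast is (m1 + m2)/2 − (m3 + m4 + m5)/3.

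| Pattern of extra loss, as a fraction of the Q1-Q5 difference | Lower group | Higher group | Contrast |
|---|---|---|---|
| Linear: 1, 0.75, 0.5, 0.25, 0 | 0.875 | 0.25 | 0.625 |
| Q1 only: 1, 0, 0, 0, 0 | 0.5 | 0 | 0.50 |
| Step: 1, 1, 0, 0, 0 | 1 | 0 | 1.00 |

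The article gives no quintile counts. With unequal shares w, a Q1-only gap appears as w1/(w1 + w2) of its size. I tried assumed shares in which Q1 is 43% (0.15/0.35) to 60% (0.30/0.50) of the lower group. The Q1-only figure then runs from 0.43 to 0.60 and the linear figure from 0.61 to 0.65.

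**3. Whether sample size explains the cut.** The cohort is described as follows: "a total of 875,934 individuals between the ages of 18 and 105 years as of 2018 were included". Prevalences of 10% (diabetes) and 4% (heart failure) come from Statistical Analysis and Power. Equal fifths are assumed. The half-width for the change within one quintile is 1.96·√(0.398/n).

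| Population | Patients per quintile | 95% CI half-width, percentage points |
|---|---|---|
| Whole cohort | 875,934/5 ≈ 175,187 | 0.3 |
| Diabetes | 87,593/5 ≈ 17,519 | 0.9 |
| Heart failure | 35,037/5 ≈ 7,007 | 1.5 |

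Even the smallest cell is about five times the plan's 1276 to 1432. The half-widths treat patients as independent; clustering within practices would widen them.

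**4. Whether power favours one contrast.** Heart failure, N ≈ 35,037, independent patients, power = Φ(z − 1.96). Effect sizes are assumptions.

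- Two groups: z = contrast / √(0.398/N × (1/0.4 + 1/0.6))
- Trend: z = slope / √(0.398/(2N)), since scores 1 to 5 have variance 2
- Q1 vs Q5: z = difference / √(0.398/N × 10)

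| Assumed pattern | Two groups | Trend | Q1 vs Q5 |
|---|---|---|---|
| Linear, 0.6 points per quintile | 59% | 71% | 61% |
| Extra 3 points in Q1 only | 59% | 71% | 80% |
| Extra 1.5 points in Q1 and Q2 | 59% | 47% | 29% |

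The ranking reverses between the first two patterns and the third.

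**The case against.** The strongest defence is that quintiles 1-2 versus 3-5 is a valid comparison of lower with higher income areas. The article labels the groups that way, and its conclusion speaks of people of lower socioeconomic status. Nowhere does it promise a gradient or a result for the poorest fifth. This stands: the contrast is not biased for what it names. It does not, however, justify withholding the five levels when the aim is to find who was affected.

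A reader might infer that the cut costs power generally and that a trend or Q1 vs Q5 should replace it. The documents do not support that. They give no expected pattern, and under a step between Q2 and Q3 the planned cut is the strongest of the three contrasts.

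A reader might also infer that a real income gap would be screened out before modelling. The article says that interactions are examined descriptively and kept if relevant. It does not say that this examination uses the two-level variable or that relevance means a significance test. The two-level cut is the only one stated for the descriptive analysis, so the inference is reasonable, but it remains an inference. The covariate is not collapsed, so an interaction could be fitted on five levels.

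Finally, the article is condensed, and further tables may be planned in a fuller document. The point therefore concerns only the grouping that the article states.

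**Conclusion.** The concern holds as a point about lost information in the planned display. With equal-sized quintiles the two-group contrast shows 62.5% of a linear Q1-Q5 difference and 50% of a gap confined to Q1. For the latter, the range is about 43% to 60% under the assumed range of quintile shares. If quintiles 1 and 2 change alike and quintiles 3 to 5 change alike, nothing is lost. A flat statement that the gap is halved would therefore claim too much.

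That all five levels are held is inferred from the variable's name and its uncollapsed use as a covariate. Cell sizes give no reason for the cut in the whole cohort or in the two exemplar conditions, though rare outcomes may be thinner. No test or sample size is invalid, and no general power gain is claimed. This is a cheap improvement.

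**What to change.** In Descriptive Analyses, present outcomes and pre-post changes with 95% CIs for each of the five income quintiles, and keep the 1-2 versus 3-5 comparison as a summary. In Analyses of Changes Over Time, state that the period-by-income interaction will be examined on the five-level variable. Report a trend across quintiles and Q1 vs Q5 as supplements to the two-group contrast, not replacements for it.

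The cost is five quintile rows beside the two already planned, with no new data if the five levels are held as the variable's name implies. Cells will be smaller for rare outcomes, where the two-group summary remains available. The Study Timeline section places the work at the exploratory stage in May 2023, so the main tables had not yet been produced when the article was written.
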